**Appendix
Study Protocol**

| TITLE  **Can Cancer Experts Accurately Forecast the Replication of Cancer Biology Trials?** |
| --- |
| INTRODUCTION  The replicability of experimental findings is a key tenant of science. There is mounting evidence that many findings in the basic and preclinical literatures cannot be reproduced.[1–4] This has important policy and ethical implications - particularly in the context where non-reproducible findings are used to launch clinical trials, costly research initiatives, or support policy.  To date, most investigations of reproducibility have used one of two different methods. First, meta-analytic tools have been used to provide evidence that effect sizes are overestimated, that there is an excess of statistically significant findings, or that effects between related studies are not concordant with each other.[5,6] A second method has involved direct and strict replication of experimental findings in order to gauge the degree to which findings are reproducible.[4] This latter approach has been used in spinal cord injury, cancer, and most recently, psychology. Together, these two streams of evidence tell us that many published reports, in diverse research areas, describe effects that are exaggerated, or in some cases, spurious.  An important limitation of this literature, however, is its focus on the experiment and its effect, rather than the beliefs they produce. Experiments are merely the substrate out of which scientific belief is produced. Experiments are conducted not for their own sake, but rather to support valid inferences about natural phenomena. Phenomena cannot be proven by individual results; instead theories are developed based on the accumulation of evidence. Non-reproducibility threatens valid inference from a scientific, policy and ethical standpoint. To our knowledge, no one has yet looked at the validity of inferences that experts make about the reliability of research findings in basic science or biomedical research.  This study will use forecast methodologies to investigate the accuracy of researchers’ judgments about the reproducibility of findings in cancer biology. In particular, we will investigate whether researchers have an accurate understanding of the replicability rate in their field, and if they have the capacity to discriminate between effects that can be confirmed and false positive results. We will also investigate whether there are certain types of individuals who are better at discriminating reproducible from unreproducible findings. By collecting forecasts from a large sample of researchers, we can also assess whether the weight of opinion in research communities is swayed - or resistant to - potentially exaggerated effects reported in studies. By investigating the inferential dimension of the reproducibility crisis, the findings of this investigation will clarify whether scientists (and the community) are savvy consumers of biomedical evidence.  Quantifying beliefs about replicability rates will have important implications for scientific methodology and policy. Results will fall between four extremes. 1) Experts accurately predict high replication rates indicating the scientific method is working and published results are high quality. 2) Experts believe replication rates are high, but they are low indicating researchers are overly trusting of published findings. 3) Experts believe replication rates are low, but they are high indicating the recent scrutiny about research methodology and/or stream of bad press sometimes describing sciences as being in “crisis” is resulting in seepage the scientific community (see [7] for an analysis of the impact of seepage on climate change research). 4) Experts accurately predict low replication rates, indicating the research community has good savvy regarding the interpretation of research findings, but researchers are exercising enough flexibility in scientific methodology to lead to an excess of significant results.  This investigation will piggyback on a project underway in cancer biology that is reproducing 50 recent^[[1]](#footnote-1)^, landmark papers in cancer biology.[8] We will collect a series of subjective probability forecasts of dichotomous outcomes from a large sample of cancer researchers on each of the experiments underway in the cancer reproducibility initiative (e.g. “what is your subjective probability that the effect size measured in the replication of experiment 5 will be as large or larger than the original effect size?”) We can then score individual researchers on their ability to discern reproducible from non-reproducible finding. We will also score the broader community, and probe whether researchers of the original reports, or possessing certain cognitive traits, are better or worse at anticipating the reproducibility of their studies.  This project is a module that fits within the parameters of our originally funded grant. We have maintained several concurrent modules testing forecast skill in basic and clinical research - all have received IRB approval. |
| PRIMARY OBJECTIVES  To determine how well the expert cancer research community, in the aggregate, can forecast the overall replication rate of high impact preclinical cancer studies and the reproducibility of specific high impact basic and preclinical cancer experiments.  To determine how well individual experts in this community can forecast the overall replication rate of high impact preclinical cancer studies and the reproducibility of specific high impact basic and preclinical cancer experiments. |
| SECONDARY OBJECTIVES   1. What are the cognitive characteristics of the experts who update more appropriately? 2. Determine whether beliefs about the pace of progress in medical research (AKA medical boomster / doomster scale score) correlates with forecast skill. 3. Determine demographic characteristics of better forecasters. 4. Determine target study features (in vivo vs. in vitro, etc) with higher forecast success rates 5. How well do forecasters update after seeing results? 6. What are the demographic characteristics of experts who update more appropriately? 7. What types of evidence do the most effective forecasters prioritize, and what study features are easiest to predict? 8. Combine several above results to identify which trial and forecaster characteristics lead to more accurate forecasts. 9. Determine whether researchers who originate a report are more or less accurate than independent experts, individuals associated with the team replicating the experiment and non-experts. |
| METHOD OVERVIEW  We will use both ‘binary’ forecast methodologies (i.e. subjective probability on binary outcomes) to collect forecasts for individual replication studies, and ‘simplified continuous’ elicitations on select studies. When replication studies close, we will collect study outcomes, determine forecast scores using a proper scoring rule (called Brier score), and collect updated forecasts. |
| SAMPLING  Study sampling and sample sizes:  Our study sampling frame will consist of all (approximately 35) studies being tested in the Reproducibility Project:Cancer Biology. We will categorize the studies based on theoretical and practical features. We will remove studies due to lack of feasibility (e.g. if there is not a clear relevant effect to predict, such as many in vitro studies especially those focused on cell signaling; if maturation date is too far in the future). We will prioritize studies whose results will be published sooner.  We will work with an independent expert to create or edit two to three questions for each study that can be rendered into dichotomized forecasts. In stage 1, participants will forecast all of the first six (all based on mouse models) studies from the cancer reproducibility project plans to publish. Participants will answer two binary elicitations for six events and simplified continuous elicitations for two events.  When mouse survival or tumor growth curves are used, questions will be created around them. When there are no mouse studies, we will shape a question around a study with a quantitative outcome. We plan to conduct a brief pilot to ensure the question types are relatively intuitive. Question formats might vary slightly depending on pilot results.  For the binary elicitation, our questions will take the two^[[2]](#footnote-2)^ of the following general forms:   1. How likely is it that the replication also be significant (at p ≤ .05)? 2. How likely is it that the effect size of the replication will be as large or larger than the original effect size?   For the simplified continuous elicitation (SCE) for the effect size of the specified treatment group, we will use a four question format, based on [9]:  1. What is the lowest effect size you realistically anticipate will be reported for study X?  2. What is the highest effect size you realistically anticipate will be reported for study X?  3. What is your best guess of the effect size you realistically anticipate will be reported for study X?  4. How confident are you (from 0% to 100%) that your estimated interval (lowest to highest) will include the reported effect size from study X?  Investigator sampling and planned strata:  All respondents will be at least 18 years old and will complete an informed consent.  Our primary sample will include two strata:  *a) Independent Experts*: we will create a sample of about 50 to 100 eligible independent international experts by compiling a list of authors from two searchers based on each original study undergoing replication: a) *related article* searches on PubMed and b) articles citing the original report. We will include corresponding authors and anyone who appears at least three times in any single search.  b) Novices: we will recruit a sample of about 50 to 100 medical undergraduate or upper level undergraduate biology majors, graduate students, or postdoctoral fellows at various universities via department mailing lists to participate in our study.  We will aim to include two secondary strata^[[3]](#footnote-3)^:  *c) Originators*: we will contact each co-author on each original research publication for an elicitation.  *d) Replicators*: we will contact each co-author on each replication protocol - only in cases where data collection has not yet been initiated.  Subjects will be approached through email (except non-experts, who may be approached in a class), and administered the questionnaire electronically.  Individuals will be approached up to five times before declaring them as having declined participation.  Sample size:  Our target sample size is as follows:  We will collect forecasts on 3 events in a half hour. We will collect 2 binary forecasts on 6 effects from 6 experiments + simplified continuous forecasts on overall replication rates). We will split the trial sample into two surveys to minimize the number of trials for which participants only have general expertise.  We will target 30 forecasts per participant on 6 events.  We will aim for 150 participants (50X2=100 independent experts + 50 novices) and expect a minimum of 90 (30X2=60 independent experts + 30 novices). |
| INTERVIEW AND DATA COLLECTION  Interviews will be conducted in 2 stages:   1. Intake interview: in one 30-minute survey presented over the internet (or in person, or by paper and pencil), we will present subjects with a one-page summary sheet describing each replication study (see Appendix 2), as well as a questionnaire (see Appendix 3). Individuals will be approached using appropriate elicitation technique, whereby we first a) describe the goals of the project and how to complete the questionnaire; b) attempt to motivate good performance by explaining how scoring works; c) provide a simple warm up question (asking for a weather forecast); d) elicit replication forecasts; and e) collect additional cognitive and attitudinal measures. The questionnaire will first collect forecasts, then individual difference variables (as applicable), then demographic variables. 2. Forecasts: subjective probabilities on target experiments.    - 1. 2 binary: Significant difference and direction on 3 replication studies      2. 2 @ 4 parameter simplified continuous (best estimate, range, confidence) on overall replication rates.    1. Individual difference variables       1. Actively Open-Minded Thinking[10]       2. Pace of progress of medical research (AKA Medical Boomster-Doomster, adapted from [11])       3. Self-report of expertise for each study       4. Confidence rating of each forecast       5. Time for forecasts       6. Evidence reliance       7. Familiarity with and Anticipated Impact of Reproducibility Project       8. Estimate of perfect replication of effect sizes    2. Demographics:       1. age       2. gender       3. expertise: H index, title/rank (associate professor, full professor, etc.), number of publications, number of citations (all collected from both SCOPUS & Web of Science), nationality/region 3. Post-event Interview: Once results are available, all participants will be approached for posterior and recalled forecasts. We will collect the first set of posterior distributions when the first batch of results is published. Once all data are collected, we participants will be debriefed about study hypotheses and offered an opportunity to learn their forecast skill against the average of their peers. |
| INCENTIVIZING GOOD PERFORMANCE  Getting good forecasts requires providing strong motivations. We will create incentives in three different ways:   1. Top scores will be posted to <http://www.translationalethics.com/forecast-scoreboard/>. We will also attempt to partner with the journal that agrees to publish our manuscript for a feature article that reports on the project, and that lists the top 5 forecasters in each expert stratum by name - provided each expert provides written consent to be de-anonymized. 2. The top two expert forecasters in each stratum will be offered awards of $200 and $50 USD, respectively. The top two novice forecasters will be offered $50 and $25, respectively. 3. We will maintain a website that lists all participants in code, and that shows each individual’s Brier skill score, and the position of their score on a distribution of brier skill scores. Individuals will be told their code so that they can check their forecast performance against others. |
| PRIMARY ANALYSIS  We will calculate the Brier scores of each individual forecaster, and present a distribution. A Brier score is a proper scoring rule – meaning it incentivizes honest reporting of subjective beliefs – which measures the accuracy of a forecast: BS = 1/N $\sum_{i=1}^{N} \left( f_{i}-o_{i} \right)^{2}$ where *f_i_* is a forecast and *o_i_* is a realized outcome for each of i events.[12] We will decompose into calibration = 1/N $\sum_{i=1}^{N} {1/n_{i}\left( f_{i}-\bar{o}_{i} \right)}^{2}$, and discrimination = 1/N $\sum_{i=1}^{N} 1/n_{i}(\bar{o}_{i}\left( 1-\bar{o}_{i} \right))$.[13] We will construct calibration curves for individual forecasters. Our null hypothesis is that mean Brier score 95% confidence intervals exclude Brier score for a matched sample size of hypothetical forecasters predicting same trials using a random number generator. We will also measure the Brier Skill Score for individuals: BSS = 1 – BS/BS_ref_ where BS_ref_ is the base rate for the reference class or of a confidence interval. The sample variance can be used when is BS_ref_ unknown.[14]  Primary endpoint   1. Replicability rate measures: The brier scores for aggregate measures will be slightly higher than .25 (note: .25 is the equivalent of a 50-50 prediction meaning “I don’t know” or a random guess). The mean forecaster will perform slightly worse than base-rates. Forecasts will be skewed toward predicting more successful replications than observed, but less than statistically expected. The order of successful predictions of aggregate replicability rates will be: 2. Effect sizes at least as large (Brier of about .20 to .25) 3. Significance (p-values) (Brier of about .25)   An a priori power analysis suggests we need a sample size of 34 to detect if expert Brier scores are different than a constant (e.g. random guessing (BS = .25) or a base rate (e.g. 80% of significant effects in cancer phase 3 trials favor the new treatment[15]) by a moderate degree (difference from a constant of Cohen’s d = .5) assuming power = .80 and alpha = .05.   1. Individual study measures: The Brier scores for individual studies will be slightly lower than .25. Forecasts will predict more successful replications than observed. Brier scores will be lower (forecasts will be more successful) for forecasting the direction of the difference between effect sizes (Outcome2) compared to forecasting significant differences (Outcome1). Base-rates will outperform the typical forecaster, but aggregating the top-tier of forecasters will beat base-rates. |
| SECONDARY ANALYSIS ON FORECAST SKILL^[[4]](#footnote-4)^  An a priori power analysis suggests we need a sample size of 34 per group to detect if detect if the experts differ from (d = .5) the novice group assuming power = .80 and alpha = .05, and we need about 180 total respondents to detect a moderate difference (f = .25) between all four strata. As analysis is exploratory, we do not intend to correct for multiple hypothesis testing.   1. Expert strata analysis: 2. The order of predicted replication rates will be: 3. Novices/Non-experts (Should be optimistic since and less attuned to the “replicability crisis” across scientific disciplines) 4. Originators (if available- should be optimistic due to their investment in these results, but more realistic than novices) 5. Independent Experts (Should be less biased due to independence from findings) 6. Replicators (if available- theoretically well attuned to flawed research design and practices) 7. The order of forecast skill will be: 8. Independent Experts (should have sufficient expertise and less biased by own work) 9. Originators (if available- should have sufficient expertise, but more myside bias) 10. Replicators (if available- assumes lab skills are higher than knowledge for this group) 11. Novices/Non-experts (assuming expertise and forecast skill are related, they have the least expertise) 12. The order of variability in forecasts will be: 13. Novices/Non-experts (assuming expertise and forecast skill are related, there should be more variability for those with the least knowledge) 14. Independent Experts 15. Replicators (if available- assumes replicators are well attuned to good and bad study design and difficulty of carrying out certain studies) 16. Originators (if available- assuming expertise and forecast skill are related, there should be less variability in recognizing real empirical relationships and flawed study design by those who have devoted their lives to studying these topics) 17. Expertise will have an inverse U-shaped (∩) relationship with forecasting success. People with low expertise will perform poorly due to inadequate information, and people with high expertise will perform poorly due to maladaptive beliefs (e.g. confirmation bias). The correlation between perceived expertise and Brier score will be ranked as follows:      1. Originators (if available- should perform when they claim higher expertise; have motivation to honestly claim high expertise for some, but not all topics) 2. Independent Experts (may be less discriminating in expertise ratings than originators since they don’t have personal relationships with any of the studies) 3. Replicators (if available) 4. Novices/Non-experts (should have consistently low expertise ratings) 5. Predictors of Forecast Skill: We will test the relationship between each demographic and scale variables and Brier Skill Score, secondarily looking at components of calibration and discrimination. The individual differences should influence the forecasts in the following order (from most to least influential). 6. More extreme updaters: Those who update more extremely relative their will have more accurate forecasts^[[5]](#footnote-5)^. 7. Pace of progress: Those who believe medical technology should progress quickly (slowly) will have more optimistic (pessimistic) forecasts. 8. Evidence reliance: 9. Those who rate the methodology of the replication attempt as important will be pessimistic. 10. Those who cite specific trial outcomes as evidence will be worse forecasters, and those who cite treatment or disease type (base rates) will be better forecasters. 11. Expertise: Those will high (self-reported and actual) expertise will be more accurate; actual expertise (H- & M-indices) will be more predictive of forecasting skill. 12. Confidence will be weakly correlated with forecasting skill. We expect a hard-easy effect where forecasters are overconfident on hard items and underconfident on easy items. 13. Demographics     1. We will also test methods of identifying forecasting skill early (prior to target event realization) the relationship between individual forecaster’s Brier scores and their average squared distance to the median compared to other baselines (mean, expectation due to chance, expectation due to base rates if available) - we hypothesize that this will lead to a strong relationship with forecast skill. 14. Aggregation of Forecasts 1: We will test whether different aggregation approaches give better forecast performance (i.e. lower Brier scores). First, to determine the relative value of using combined forecasts to make decisions, we will construct a curve of showing the relationship between Brier scores and number of aggregated forecasts. Specifically, the curve will reflect n=0 aggregation (i.e. average Brier scores of individual forecasters); n=1 (i.e. average Brier score when two forecasters forecasts are randomly aggregated); n=4 (i.e. average Brier score when 5 randomly selected forecasts are aggregated); and n=9 (i.e. average Brier score when 10 randomly selected forecasts are aggregated). We will also use transformations to make predictions more extreme.[16,17] 15. Predictors and Aggregation: Using individual differences and demographic variables that show low skill identified in step 1, we will test the competitiveness of aggregated low skill forecasters with the individual scores of high skill forecasters. For instance, suppose we find a relationship between high M-index and high forecast skill. We will then test whether, if we combine forecasts from 2, 3, 5 and 10 low M-index forecasters, on average the forecast outperforms the average forecast of high M-index forecasters.   After we have completed forecast scoring, we will also rank all individual forecasters by their Brier skill scores, and randomly select individuals within tiers of upper, middle, and lower thirds. We will test whether combined forecasts of 2, 3, 5 and 10 “low skill” forecasters can, on average, beat the forecast of randomly selected individuals from each skill tier. Brier scores will be used; as well, they will be decomposed into discrimination and calibration. |
| SECONARY ANALYSIS ON UPDATING AND RECALL   1. Updating: To determine the extent to which researchers properly update belief (as opposed to stubbornly clinging to their priors - or abandoning them), we will perform all primary and secondary analyses, scoring elicited posteriors against proper posteriors (calculated on the basis of Bayes’ Theorem using a beta distribution). |
| ETHICS  Issues: This study presents two human subject issues:  1. Subject burden: this study will require a 30-minute intake interview for approximately 110 researchers and 50 students; this will be followed up a year later or so with a debrief interview lasting no more that 20 minutes. This is a large commitment of time for busy researchers.  2. Confidentiality: What a researcher believes about an experiment or his or her forecast skills constitute sensitive information. We will strictly protect the confidentiality of all participants as well as their scores, as explained by the measures below  Protections:  1. General: Protocol will be submitted for independent ethical review prior to initiation. Informed consent will be obtained from all participants prior to data collection, and documented upon signing the questionnaire or initialing a consent box in the electronic interface.  2. Subject burden: We will minimize burden by minimizing sample size and streamlining interviews. Informed consent will be obtained; as scientific researchers are not a vulnerable population, we are confident they can protect their interests by deciding whether to participate. No students who are approached for participation will be enrolled in a class taught by the individuals on this protocol.  3. Confidentiality: All participants will receive a numeric identifier that is used to label all responses. The key linking participant identity to data will be maintained in a locked filing cabinet and a password protected computer. The key will be maintained only to enable recontact of investigators in the event of a follow-up study. Key and all identifying information will be destroyed within five years of data collection. All identifying information will be maintained in strict confidence.  The ‘best’ forecaster will be identified by the research team and notified as such. He or she will be given the option of being de-identified and profiled on the STREAM website. His/her permission to de-identify will be documented with a signature. |
| APPENDICES   1. Map of survey versions 2. Sample information sheet for Replication Study 3. List of replication studies |

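### Outcome 2 is a valid event to forecast, but it is labelled a replicability rate with no reference rate, although perfectly reproducible studies would meet it only about half the time or less.

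*Protocol*

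**What the plan says.** The SAMPLING section of the protocol defines two binary questions per study. Outcome 1 is "How likely is it that the replication also be significant (at p ≤ .05". Outcome 2 is "How likely is it that the effect size of the replication will be as large or larger than the original effect size". The Sample Information Sheet repeats both, and neither place gives Outcome 2 a margin or tolerance.

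Outcome 2 is described in more than one way:

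- The INTRODUCTION uses it as its example question and continues: "We can then score individual researchers on their ability to discern reproducible from non-reproducible finding".
- PRIMARY ANALYSIS, under the replicability rate measures of the primary endpoint, introduces a list with "The order of successful predictions of aggregate replicability rates will be" and puts "Effect sizes at least as large (Brier of about .20 to .25" at the head of it, before significance.
- The same section, under individual study measures, hypothesises "Forecasts will predict more successful replications than observed". It then describes Outcome 2 more neutrally, as "forecasting the direction of the difference between effect sizes (Outcome2".

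INTERVIEW AND DATA COLLECTION lists "Estimate of perfect replication of effect sizes" among the individual difference variables. PRIMARY ANALYSIS also expects forecasts to lie below a statistical expectation, but gives that expectation neither a value nor a definition.

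**The concern.** The Outcome 2 cutoff is itself an estimate with sampling error. A replication of a real effect of exactly the same size will often fall short of it by chance. A low observed Outcome 2 frequency is therefore what perfect reproducibility would also produce.

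Once the outcome is called a replicability rate, two conclusions become too easy. One is that a shortfall shows the studies did not replicate. The other is that forecasts above the observed frequency show experts trusting too readily that findings are real. The hypothesis that forecasts exceed observed successes would tend to be confirmed on Outcome 2 by any mean forecast above 50%, even if every study were reproducible.

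**Working it through.** **Inputs from the protocol.** The Outcome 2 cutoff is the original point estimate. Outcome 1 is p ≤ .05. There are six studies, three per expert survey (Survey Versions). The reference Brier score is .25.

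**Assumptions, not in the protocol.** The two estimates are independent and symmetric around the same true effect. Where selection is considered, an original is kept only if z > 1.96. Original power π is 50%, 80% or 90%, and standard errors are equal unless stated.

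**1. The plan's own figure.** A constant 50% forecast scores (.5 − o)² = .25 whether o is 0 or 1. The protocol's .25 is reproduced.

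**2. Success rate without selection.** Replication minus original has mean 0 and variance SE_o² + SE_r², so P(difference ≥ 0) = .50 for any pair of standard errors. The same holds if the true effect equals the original estimate exactly. Simulation with two million pairs gave .499 to .501. For a standardised effect in small unequal groups (assumed d = 1.5) the rate was .48 to .51.

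**3. Success rate when originals were selected for significance.** With equal standard errors, a selected original that is matched or exceeded requires both estimates to pass 1.96, which has probability π². By symmetry the replication is the larger in half of these cases. Dividing by the selection probability gives

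P = (π²/2)/π = π/2.

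This is .25, .40 and .45 at π = .50, .80 and .90. Simulation gave .250, .400 and .45. With a replication four times larger the rates were .15 at π = .50 and .38 at π = .80, so more replication data does not restore the rate.

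**4. Six fully reproducible studies at 50%.** P(two or fewer successes) = (1 + 6 + 15)/64 = 22/64 = .34. P(three or fewer) = 42/64 = .66. For the three studies in one expert survey, P(one or none) = 4/8 = .50.

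**5. Attainable Brier scores.** For an event of probability P and forecast q, the expected score is P(1 − q)² + (1 − P)q². It is smallest at q = P, where it equals P(1 − P). With equal standard errors and the same true effect, replication power is also π, so:

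| π | Outcome 1: P | Outcome 1 floor | Outcome 2: P, selected | Outcome 2 floor |
| --- | --- | --- | --- | --- |
| .50 | .50 | .25 | .25 | .19 |
| .80 | .80 | .16 | .40 | .24 |
| .90 | .90 | .09 | .45 | .25 |

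Without selection, Outcome 2 has P = .50 and a floor of .25 in every row. The floors of the two outcomes differ, and their order changes with π. A comparison of mean Brier scores between the outcomes therefore partly reflects the two thresholds and not only forecasting skill.

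**The case against.** The strongest reply is that Outcome 2 is asked in plain words, is a well-defined event and is scored by a proper rule. That stands. At P = .50 a forecast of 80% expects .5(.04) + .5(.64) = .34, against .25 for a forecast of 50%. A reader might infer that experts who believe in a real effect are penalised unfairly. They are not: an 80% forecast of a 50% event is miscalibrated, and the score should show it.

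A reader might also infer that even perfect knowledge cannot beat .25 on Outcome 2. That holds only at P = .50 exactly. The floor is P(1 − P), which is .24 at P = .40 and .19 at P = .25, so the protocol's predicted range of .20 to .25 is compatible with attainable values.

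Detecting exaggerated published effects is a stated aim in the INTRODUCTION. Under selection, expecting an inflated estimate to be matched is a real error about effect size. This stands too, but it supports reading Outcome 2 as relative effect size, not as a verdict on whether a finding is real. Outcome 2 does carry some information on the latter: for a spurious effect selected as significant in the claimed direction, π = .025 and P = .0125. But the 50% to 75% of fully reproducible effects that also fail make a failure weak evidence.

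The protocol shows partial awareness. It uses the neutral description, mentions a statistical expectation, allows base-rate references for the skill score and collects the perfect-replication item. SECONDARY ANALYSIS ON FORECAST SKILL tests demographic and scale variables against skill, so it would be wrong to say the item has no planned use. What is missing is its use as a benchmark, and any stated rate for Outcome 2 under exact replication. The only numerical base rate offered is the 80% example from phase 3 trials. A statistical analysis plan not seen here might add the benchmark, but the replicability label is set in the protocol.

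Finally, the INTRODUCTION's remark about excessive trust concerns replication rates and does not name Outcome 2, and significance always sits beside it. The protocol does not commit itself to the wrong conclusion; it leaves the way open to it.

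**Conclusion.** The point holds as one of labelling and reference. Under perfect reproducibility the Outcome 2 success rate is 50% without selection and lower with it: about 25%, 40% and 45% at original power of 50%, 80% and 90%. The 50% rests on independent, symmetric estimates of one effect. The lower figures also rest on the assumed power, equal standard errors and selection at p ≤ .05. The protocol's INTRODUCTION acknowledges excess significance in the literature but does not quantify it for these six studies.

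A shortfall on Outcome 2 alone therefore cannot be read as non-reproducibility, or as misplaced trust that findings are real.

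A reader might conclude that every reproducibility claim must rest on Outcome 1. The documents do not support that as a requirement. Outcome 1 also misses true effects by chance, 20% of the time at 80% power, and dropping Outcome 2 would leave one binary result per study. That is a debatable trade-off.

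**What to change.** - In PRIMARY ANALYSIS, label Outcome 2 as relative effect size, using the protocol's own description as the direction of the effect-size difference, and take it out of the replicability rates.
- Report the mean Outcome 2 forecast and the observed frequency against 50%, stated as an upper bound if originals were selected for significance.
- Report both also against each respondent's own estimate for perfect replication of effect sizes, which the survey already collects.
- State that an Outcome 2 shortfall alone will not be read as non-reproducibility or as over-trust in whether findings are real.
- Where Brier scores of the two outcomes are compared, note that their floors, P(1 − P), differ.

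The survey, sample and scoring rule do not change. The cost is one extra comparison and a narrower reading of one of the two primary binary outcomes.
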